### Adverse events and monitoring of possible harms

These are enumerated and defined time frames for monitoring and reporting as specified in Table 5. Most guidance would recognise hospitalisation, or prolongation of hospitalisation, and death as serious adverse events, requiring prompt reporting to regulatory bodies. However, both of these events are expected to occur frequently among adults on ART. Based on follow-up from our previous trial in a similar ART population, we expect a mortality rate as high as 5% during the 12-month follow-up period, and a hospitalisation rate of approximately 10% [40]. We expect much of this mortality and morbidity to be due to the underlying HIV infection, advanced enough to warrant treatment with ART prior to the introduction of universal treatment. Systematic monitoring of hospitalisations and deaths is planned, but will be episodic, occurring at the 6- and 12-month follow-up participant interviews, and with quarterly linkage of hospitalisation and once-off linkage with the national population register data. Given that these events, while serious, are common in this population, are likely to be related to the underlying HIV disease progression, and that monitoring is episodic, we have proposed that the frequency of these events be reviewed 6 monthly by the Data and Safety Monitoring Board (DSMB), and then reported to the relevant Institutional Review Boards (IRBs) (University of Cape Town, University of Kwazulu-Natal and King’s College London), with the DSMB Letter of Recommendation. Because suicide may well be related to a mental health intervention, and is likely to be rare, we report any such events within 7 days of the knowledge of the event in accordance with the recommended Standard Operating Procedures of the University of Cape Town’s IRB. All deaths will be followed up with clinic staff and family members to determine whether or not they were the result of suicide.

A further serious adverse event that is unlikely to be related to the intervention, but which may occur as a result of participation in the data collection component of the trial, is a markedly elevated viral load in the context of pregnancy, placing the foetus at risk of transmission. For this reason, it will be managed as a serious adverse event and reported to the IRB and DSMB within 7 days. We follow-up all viral loads in excess of 1000 copies/mL to see whether or not they appear to be reported during pregnancy and we urgently pursue all missing viral loads in women who report themselves to be pregnant. Once we confirm a high viral load in a pregnant woman, we immediately notify the clinic staff and advise them to recall the women urgently for clinical care and intervention to limit transmission of HIV to the baby.

We report non-serious adverse events to the DSMB 6 monthly. We ask the participants who respond positively to the ninth item of the PHQ-9 “Thoughts that you would be better off dead or of hurting yourself in some way” to confirm their answer and, if they indicate having such thoughts between 1 and 7 days in the last 2 weeks, we provide them with written educational material on suicide prevention. If they confirm having such thoughts for 8 days or more in the past 2 weeks, we immediately refer them to clinic staff for review. This protocol applied to the pre-screening process even for patients who responded positively to the ninth item of the PHQ-9 but were otherwise not eligible for enrolment in the trial. Likewise, we immediately refer participants with a blood pressure of ≥ 180/110 to clinic staff for review of their blood pressure. Once data collection is complete, we will present a summary of adverse events to clinics together with recommendations for further treatment. These adverse events are a PHQ-9 score of ≥ 20, suggestive of severe depression, raised blood pressure at follow-up representing undiagnosed or uncontrolled hypertension, and detectable viral load at follow-up representing possible adherence problems or treatment failure.

### Cost-effectiveness economic evaluation and modelling of long-term costs and effects

We will use the adapted Service Utilisation Questionnaire to systematically collect resource-use data, including any inpatient care, consultations with health providers, use of medications and laboratory tests, and time and travel costs associated with service uptake. We will collect information on the financing sources for each of the service categories to allow for an estimation of the extent of private, out-of-pocket expenditures incurred by recruited participants and their families. The unit costs or prices of these various resource inputs will be taken from previously conducted costing studies in South Africa [81] and from WHO-CHOICE data [82]. We will obtain medication costs from the Primary Care Guideline App published by the National Department of Health in South Africa [83]. Time loss from work may be affected by the interventions and we will measure this at baseline and follow-up and will value it using average wage rates. We will add the above costs to those of the actual intervention, which will be determined using an ‘Active Ingredients’ approach and allocated to trial participants using responses derived from the Service Utilization Questionnaire and linkage to related databases (e.g. counselling records). We will derive these from activity data (session provided per patient) and therapy unit costs (based on salaries, overheads and working hours). We will then make cost comparisons using bootstrapping methods to account for likely skewness in the data distributions.

To examine issues of cost-effectiveness, we will first relate estimated service costs per case in the different arms of the trial to primary study outcomes (viral loads and PHQ-9 scores). Based on earlier studies of stepped care for depression in India [84], a decrease in overall resource use can be expected due to a drop in ineffective but financially burdensome visits to providers unqualified to offer appropriate depression care. Since health outcomes for the stepped care intervention are also expected to improve significantly, the intervention will ‘dominate’ usual care (i.e. better outcomes, less cost); such a hypothesis negates the need for a power calculation. If, however, costs are found to be higher in the intervention group, bootstrapped incremental cost-effectiveness ratios for PHQ-9 depression and viral load scores will be derived. Irrespective of whether point estimates demonstrate dominance, results will be plotted on a cost-effectiveness plane and presented as cost-effectiveness acceptability curves in order to show the probability of the intervention being cost-effective at a range of ‘willingness-to-pay’ threshold levels. We will conduct sensitivity analysis to take account of uncertainty and imprecision in the measurements, including multiple imputation models for missing values.

As a second stage, we will move beyond the time and space constraints of the trial and consider longer-term costs and effects of the trial intervention at the population level. For this, we will construct and populate a quantitative economic model of expected lifetime costs and health gains, based on the earlier Markov modelling studies of Bachmann [85] and Cleary [81], but adapted to better capture other health states and outcomes of interest (depression and other NCDs, in particular cardiovascular disease and diabetes). We will convert health improvements observed in the trial into years of healthy life gained at the population level in the newly developed mental, neurological and substance use module of the inter-UN OneHealth strategic planning and costing tool [86], specifically by multiplying observed effect size for the intervention by the target rate of treated prevalence in the population. We will similarly compute population-level costs in OneHealth by multiplying the resource use and cost per case by the number of cases treated in the population at target coverage levels.

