
### Randomisation, allocation concealment and blinding

We randomised clinics and their patients to one of two parallel groups, with an allocation ratio of 1:1. Within each district, we considered the distribution of clinics within sub-districts to ensure that we did not introduce potential confounding through geographically determined management of clinics. Within the [name] district, 12 clinics fall within the Matlosana sub-district in the area, including and surrounding the major town of Klerksdorp, and have been randomised as one stratum. The remaining eight clinics are situated in more rural areas and randomised together. Within the Bojanala district, 10 clinics are in the central district of Rustenburg in and around the town of the same name and are randomised in a 1:1 allocation. The remaining 10 clinics are distributed over a far wider area than in [name] district and spread across the three sub-districts of Moretele, Kgetleng River and Madibeng. We combined two of the smaller sub-districts (Moretele and Kgetleng River) into one, so that we have two strata each with five clinics available for randomisation. We randomly selected one of these strata to have three intervention clinics to two control clinics, and vice versa in the other stratum, so that we have 10 intervention clinics and 10 control clinics in the Bojanala district. The trial statistician carried out randomisation using n-Query advisor prior to the intervention or screening of participants for recruitment. Blinding of participants and clinicians is not possible because it will be clear which clinics will be implementing what interventions. The trial statistician who carried out randomisation did not know the characteristics of the clinics being randomised, and the primary statistical analysis will also be blinded to allocation status.

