### Statistical methods

We will estimate the effects of the intervention by comparing the outcomes of intervention and control group patients using multiple mixed effects regression models, with clinics as a random effect to account for the intra-cluster correlation of outcomes. We will include the stratum as a covariate in the regression models, and will use Stata statistical software for the analysis. All clinics and patients will be analysed in the treatment group to which they were randomly assigned. We will ascertain the completeness of follow-up by group to evaluate the integrity of the planned analysis. We will use binomial regression to estimate differences in proportions of patients with suppressed viral loads and who have responded in terms of their depressive symptoms, measured using the PHQ-9. We will analyse secondary outcomes as follows: binomial regression for binary outcomes, linear regression for changes in depression scores, blood pressure, weight, and waist circumference by comparing values at follow-up adjusted for baseline values, and Poisson regression for count outcomes such as clinic visits and inpatient days, accounting for individuals’ duration of follow-up.

Planned secondary analyses include analysis of primary outcomes stratified and adjusted for treatment severity, treatment status and comorbidities at baseline. We will also explore whether there is a differential effect among those patients who reported receiving the counselling intervention.

The economic evaluation will include descriptive statistics describing the health system and societal costs of living with HIV and depression, a cost effectiveness analysis, and modelling of the intervention beyond the timeframe of the study.

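### The Poisson models for clinic visits and inpatient days leave out the baseline utilisation that the trial collects, which forgoes some precision; the cost bootstrap should be specified to use it too

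*Protocol article*

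**What the plan says.** In the protocol article, Statistical methods, one sentence sets the models for the secondary outcomes. Depression scores, blood pressure, weight and waist circumference are analysed by linear regression "by comparing values at follow-up adjusted for baseline values". Utilisation is analysed by "Poisson regression for count outcomes such as clinic visits and inpatient days, accounting for individuals’ duration of follow-up". The same section applies to regression models generally when it says "We will include the stratum as a covariate in the regression models" and puts clinic in the models, "with clinics as a random effect to account for the intra-cluster correlation of outcomes". The count models therefore carry stratum and clinic, but no baseline count.

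Table 4 marks healthcare utilisation and productivity as measured at baseline and at 12 months, with an incidence rate ratio as the utilisation metric. On time lost from work, the economic section adds "we will measure this at baseline and follow-up". For the comparison of costs it states only: "We will then make cost comparisons using bootstrapping methods to account for likely skewness in the data distributions". It names no covariate and no resampling unit.

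**The concern.** Use of health services before follow-up often predicts use during follow-up, both between patients and between clinics. The plan has this value for every participant and applies the same device to four other groups of outcomes, yet the counts receive only a follow-up-time adjustment. With 40 randomised clinics, chance differences in prior utilisation between arms can remain. Adjusting for baseline would remove part of them and narrow the intervals.

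The economic results are where this could count. The article makes no power calculation for costs because it expects the intervention to dominate, and it will present a cost-effectiveness plane and acceptability curves. Those displays reflect the uncertainty of the cost difference directly.

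**Working it through.** **Plan's own figure.** The article gives no figure for the precision of costs or counts, so there is none to reproduce. As a check on the design inputs, take the viral load calculation: 65% v 75%, 20 clinics per arm, 40 patients per clinic after 20% loss, ICC 0.04. The design effect is 1 + 39 × 0.04 = 2.56, the effective size is 800/2.56 = 312.5 per arm, and power is 78.0% against the stated 80%. The inputs are read correctly.

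**Inputs.** k = 20 clinics per arm and m = 40 patients per clinic (Sample size). ICC 0.04 is the viral load planning value, borrowed here for utilisation and cost. The baseline-to-follow-up correlations r_p (patients within clinics) and r_c (clinics) are assumptions.

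**Standard error of the arm difference, in SD units.**
- Unadjusted: √[2(1 + (m − 1)ICC)/(km)] = √(2 × 2.56/800) = 0.080.
- Adjusted: √{2/(km) × [(1 − ICC)(1 − r_p²) + m·ICC·(1 − r_c²)]}, where 1 − ICC = 0.96 and m·ICC = 1.6, which sum to 2.56.

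| r_p, r_c | Adjusted sum in brackets | SE ratio | SE reduction | Simulated SE ratio |
|---|---|---|---|---|
| 0.1, 0.1 | 2.56 × 0.99 | 0.995 | 0.5% | not run |
| 0.3, 0.3 | 2.56 × 0.91 | 0.954 | 5% | 0.96–0.98 |
| 0.5, 0.5 | 2.56 × 0.75 | 0.866 | 13% | 0.90–0.91 |
| 0.5, 0.8 | 0.72 + 0.576 = 1.296 | 0.712 | 29% | 0.76–0.81 |

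When the two correlations are equal the ratio is √(1 − r²) whatever the ICC. For the last row it runs from 0.80 at ICC 0.01 to 0.66 at ICC 0.10. The formula treats the slopes as known. The simulation fits stratum and baseline to 40 clinic means in five strata and shows smaller gains. Both work on a difference in means, so for a rate ratio they are a guide only.

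**Chance imbalance at baseline.** With 50 per clinic, the SD of the arm difference is √[2(1 + 49 × 0.04)/1000] = 0.077 SD: possible, but modest.

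**Stratum.** Two strata of five clinics are split 3:2 and 2:3. Over 20 clinics per arm, ignoring stratum shifts the contrast by (3/20 − 2/20) = 1/20 of the difference between those two strata, in a direction drawn at random. In the simulation, adding stratum left the true sampling SD unchanged (ratio about 1.00). What changes is the estimated SE. If strata explain a share s of the between-clinic variance, the correct SE is √[(0.96 + 1.6(1 − s))/2.56] of the unstratified one: 0.97, 0.90 and 0.83 at s = 0.1, 0.3 and 0.5. An interval that ignores strata is thus too wide.

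**Resampling unit.** If patients were resampled without regard to clinic, the SE would be 1/√2.56 = 0.625 of the correct one. The article does not say that this will be done, but it is a good reason to name the unit.

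**The case against.** A reader might infer that costs are to be compared without stratum or baseline values. The article does not say so. Bootstrapping is a method of inference and can be run around a regression with any covariates; none is excluded, and a separate publication on the economic evaluation is planned. On costs this is silence, which an article may leave to a fuller plan.

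A reader might also infer that the 3:2 and 2:3 allocation ("three intervention clinics to two control clinics" in one stratum, the reverse in the other) leaves costs open to imbalance. It does not in any material way, because the two strata offset each other.

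Nor is a large gain shown. Clinic correlations of 0.5 to 0.7 and patient correlations of 0.3 to 0.5, with ICC 0.02 to 0.10, give a variance reduction of 16% to 45%. That arithmetic is right, but the assumptions start high. Low correlations are plausible: the article expects only about 10% of patients to be hospitalised, and the cost of the intervention itself has no baseline counterpart.

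The strongest objection is timing. Patients were enrolled about two months after staff training, so baseline recall may include some exposure, in one arm only, and adjusting for it could remove part of an effect. This stands as a caution. It is limited because the embedding period was chosen partly so that patients would probably not yet have been exposed, and because the outcomes that the plan already adjusts have baselines from the same time. It is the reason to show the unadjusted-for-baseline result too.

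**Conclusion.** The point holds for the utilisation counts: the stated Poisson models leave out a baseline value that is collected, although neighbouring outcomes in the same sentence are adjusted. This is a loss of efficiency in secondary and economic outcomes. It is not a bias, and chance imbalance would not by itself settle the economic result.

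The size depends wholly on assumed correlations. At ICC 0.04 the variance reduction by formula is 1%, 9% and 25% at r = 0.1, 0.3 and 0.5. It is less in simulation at the last two, and larger only if clinics keep their utilisation levels closely from baseline to follow-up. For costs the point is a request to specify. Leaving out stratum there would mainly make intervals too wide and would not bias the comparison.

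**What to change.** 1. Add each patient's baseline utilisation to the Poisson models for clinic visits and inpatient days, beside the stratum, clinic and follow-up-time terms already planned.
2. State that the cost bootstrap is run around a regression with stratum and baseline utilisation or cost, and that it resamples clinics within strata.
3. Report the result adjusted for stratum only next to the baseline-adjusted one, because baseline recall may cover some weeks after the intervention began.

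This is analysis wording only: no new data and no change to the conduct of the trial. The statistical price is about one degree of freedom, plus the timing caution that the third step makes visible.

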### Sample size

We calculated the sample size for a superiority trial because we hypothesized that the intervention would lead to reduced depressive symptoms for patients on ART with comorbid depression, which would in turn positively influence their adherence to ART and care, and improve their HIV outcomes. We based our estimates of viral load suppression on data from our previous RCT on task-shifting HIV care in which 70% of ART patients had suppressed viral loads at follow-up with an intra-clinic correlation coefficient (ICC) of 0.046 [40]. We assumed that rates of viral load suppression will be slightly lower in a group of patients suffering from depression (65%) as it is a known risk factor for poor adherence [18, 70]. A sample size of 2000 participants from 40 clinics (50 patients per clinic, 1000 per group) provides 80% power to detect a 10% difference in 1-year viral load suppression at the 5% significance level assuming an ICC of 0.04 and a 20% loss to follow-up based on a previous trial in this setting [38]. To determine the appropriate parameters for the PHQ-9 sample size calculation we searched PubMed for all RCTs which had used the PHQ-9 as an outcome. Of the 126 trials screened, we identified nine as relevant to the design of our trial [71–79], including four cluster trials and five individually randomised studies. The trials used a mix of metrics, including difference in means, response and remission rates, measured at a range of time points. We disregarded several of the trials because their baseline scores were far higher than those we had observed in our population of interest during the validation of the Setswana localisation of the PHQ-9. We instead based our sample size estimates on three cluster trials completed in the Netherlands [71], Italy [77] and the UK [79], where PHQ-9 response rates at 6 months were reported and where baseline scores were similar to what we anticipated. Only two of the five cluster trials reported an ICC [71, 79] and, in one of these, it was uninterpretable because of very small cluster sizes [71]. We then completed a series of calculations to determine power to detect a difference of between 10% and 12% in response rates at 6 months, with the number of clusters and cluster size fixed by the viral load calculation at 40 and 50, respectively (Table 6). We allowed for the proportion of those who responded in the control group to vary between 30% and 35%, for the ICC to vary between 0.02 and 0.04 (we assumed lower ICCs were likely given that the PHQ-9 is a health outcome) and for a loss to follow-up rate of 20%. This showed that a sample of 50 patients in 40 clusters (1000 per group) yielded a power of between 73% and 96% to detect a difference of between 10% and 12% in response rates at 6 months.

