### Data management

Interview data is uploaded as soon as questionnaires are completed, internet connectivity permitting, and stored in a secure SQL server at the Trial Co-ordinating Centre at the University of Cape Town Lung Institute. We integrate data from interviews with those from other sources to create a longitudinal record for every patient participant (Fig. 5). These other sources include blood results for the viral load samples drawn as part of the research process as well as routinely monitored viral loads which are collated in a central national repository. We search hospitalisation records quarterly and integrate linkages into the research dataset. We maintain a separate database of patients referred to facility-based counsellors and link their attendance of sessions with the trial patient database. The research version of the national population register, curated by the South African Medical Research Council, will be linked once at the end of the study to identify any deaths which had not already been identified through follow-up of patients who did not return for their 6- and 12-month interviews.

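### Multiple imputation is planned only as a sensitivity analysis, so the base-case cost-effectiveness result appears to rest on non-imputed data despite an expected 20% loss to follow-up

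*Protocol article*

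**What the plan says.** The relevant section of the protocol article is the one on cost-effectiveness and long-term modelling. Its main analysis is a bootstrap comparison of costs: "We will then make cost comparisons using bootstrapping methods to account for likely skewness in the data distributions". Costs are then related to the two primary outcomes through incremental ratios, a cost-effectiveness plane and acceptability curves. Missing data appear once, at the end of that description: "We will conduct sensitivity analysis to take account of uncertainty and imprecision in the measurements, including multiple imputation models for missing values".

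Other sections supply the context:

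- **Sample size** assumes "a 20% loss to follow-up based on a previous trial in this setting" for the viral load outcome, and uses the same 20% for the PHQ-9 outcome.
- **Adverse events and monitoring of possible harms** states that "we expect a mortality rate as high as 5% during the 12-month follow-up period".
- **Patient-level outcomes, Table 4** marks healthcare utilisation and productivity at baseline and 12 months, with the 6-month cell empty. The source of utilisation is self-report plus linkage with hospitalisation databases; productivity is self-reported.
- **Patient-level outcomes** sets the primary PHQ-9 response at 6 months and viral suppression at 12 months.
- **Data management** says: "We search hospitalisation records quarterly and integrate linkages into the research dataset". Counselling attendance is linked from a separate database, and deaths are sought through follow-up and a single register linkage at the end.

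**The concern.** A sensitivity analysis varies a base case. If imputation is the variation, the base case is most naturally read as using only what was observed. Three features of the trial make this matter.

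First, the costs that only the patient can report (consultations with other providers, travel, lost work) depend on attending the 12-month interview. The article expects the intervention to save money by reducing visits to providers not qualified to give depression care, and with the sources named, that saving is visible mainly through self-report.

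Second, the PHQ-9 effect is measured six months before the costs are complete, so the sample behind the PHQ-9 cost-effectiveness ratio can differ from the sample behind the PHQ-9 effect.

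Third, the trial hypothesises better adherence to care and lists programme retention as an outcome. If the intervention does change retention, missingness will differ by arm, and that can bias the incremental cost. The second-stage population model multiplies trial cost per case, so any such bias would carry forward.

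**Working it through.** **The plan's own figure.** The article gives no figure for missing economic data. The 20% loss is used only for power. For viral suppression, 65% against 75% with 20 clinics per arm, 40 patients per clinic after loss and ICC 0.04: design effect 1 + 39 × 0.04 = 2.56; effective n per arm 800 / 2.56 = 312.5; power 78.0%, close to the stated 80%. The 20% is therefore a working assumption of the trial, applied to a 6-month outcome and to a 12-month outcome.

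**Expected counts.** 0.20 × 2000 = 400 patients lost; up to 0.05 × 2000 = 100 deaths. The article does not say whether the deaths are included in the 20%.

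**Patients with both a 6-month PHQ-9 and 12-month self-reported costs, at 20% loss per visit.**

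- Losses fully overlap (the same patients miss both visits): 0.80 × 2000 = 1600 (80%).
- Losses independent: 0.80 × 0.80 = 0.64, or 1280 patients (64%).

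Patients who die or move away before 6 months miss both visits, so some overlap is expected. The 64% is a lower illustration, not a forecast.

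**Effect on mean cost in one arm.** Let q be the share missing and R the mean cost of missing patients relative to observed ones. Then complete-case mean / all-patient mean = 1 / [(1 − q) + qR]. R is not in the documents, so a range is shown.

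| R | q = 20% | q = 5% |
|---|---|---|
| 0.5 | 1.11 | 1.03 |
| 1 | 1.00 | 1.00 |
| 1.5 | 0.91 | 0.98 |
| 2 | 0.83 | 0.95 |
| 3 | 0.71 | 0.91 |

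At 20% missing, mean cost is overstated by 11% if R = 0.5 and understated by 17% if R = 2.

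**Effect on the difference between arms.** Take observed means of 100 in both arms, so that complete cases show a difference of 0, and the same R in both arms.

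- Missing 20% in each arm: the true difference is 0 for every R.
- Missing 25% control and 15% intervention, R = 2: control 100 × (0.75 + 0.50) = 125; intervention 100 × (0.85 + 0.30) = 115; true difference −10.
- Same missingness, R = 0.5: control 87.5; intervention 92.5; true difference +5.
- Same missingness, R = 3: control 150; intervention 130; true difference −20.

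The missingness split is an assumption for illustration.

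**The case against.** The strongest reply is that the article never says incomplete patients are excluded. It is a condensed account, a separate publication is planned for the economic evaluation, and a base-case missing-data rule is commonly left to an analysis plan that is not shown. That stands as far as silence goes: the absence of a rule is not the point here. The point rests on what is stated, namely that imputation is given a sensitivity role. A reader might infer that the main result definitely drops everyone with incomplete data; the text makes a non-imputed base case the natural reading and no more.

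A reader might also infer that the patients lost are those who died or left care, that they are the costliest, and that costs are therefore understated. Nothing in the article supports this. Patients who leave care may use fewer services, and those who die early accrue cost for less time, with zero rather than missing cost afterwards.

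Similarly, with the article's 10% hospitalisation rate, one could assume that non-attenders are admitted 2 to 3 times as often. Solving 0.8r + 0.2kr = 0.10 gives 8.3% (k = 2) or 7.1% (k = 3) among attenders, an apparent understatement of inpatient use of 17% to 29%. The multiplier is not in the documents, and the result applies only if the planned hospital linkage is ignored. Inpatient and counselling costs are the components that depend least on interviews.

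Two further limits stand. The timing mismatch affects the PHQ-9 ratio but not the viral load ratio, whose outcome is at 12 months. And the section on recruitment and data collection describes follow-up interviews as covering utilisation and economic outcomes without separating the two visits, so the 12-month-only reading rests on Table 4. Even if some costs were also taken at 6 months, a patient missing the 12-month visit would still lack self-reported costs for the second half-year.

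Finally, the imputed result will be reported in any case, so a discrepancy would be partly visible. That lowers the stakes, but leaves two possible answers with the non-imputed one as the headline.

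**Conclusion.** The point holds in a limited form. As written, the base-case cost-effectiveness result appears to rest on non-imputed data in a trial that expects 20% loss, with self-reported costs complete only for those seen at 12 months. At an assumed 20% loss per visit, 64% to 80% of the 2000 patients would have both the 6-month PHQ-9 and those costs. Mean cost may be biased in either direction. Incremental cost is biased if missingness, or the costs of missing patients, differ by arm, for example through better retention in the intervention arm. The documents fix neither the size nor the sign; the figures for R and for unequal missingness are illustrations. Cost-effectiveness is a secondary objective, and the co-primary analyses are unaffected, so this is a worthwhile and inexpensive improvement rather than a threat to the trial's main conclusions.

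**What to change.** Reverse the roles of the two analyses and state this before economic results are seen:

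1. Define the base case as all enrolled patients in their allocated arm.
2. Take inpatient use and counselling contacts from the linkages already planned, for every patient and not only those interviewed.
3. For patients who die, count costs up to the date of death and zero afterwards.
4. Multiply impute the remaining costs and outcomes separately by arm, with clinic and stratum in the imputation model.
5. Report the complete-case result beside it as the sensitivity analysis.

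No new data are needed. The cost is a few sentences in the analysis plan and some analyst time. The downside is that the base case then relies on a missing-at-random assumption, which the complete-case comparison would help readers to judge.
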